#### Patient reported outcomes

Patient reported outcomes (QLQ-C30, QLQ-HCC18) to be collected at 6 monthly intervals post-randomisation (e.g. 6, 12, 18, 21, 24, 30, 36 months).

## Progression

Once progression has been confirmed on abdominal imaging, completion of restaging with a CT chest (+/- pelvis) is required within 2 weeks.

On-trial assessments should continue beyond progression to allow for collection of subsequent therapies, QoL, and second sites of progression to aid primary and secondary endpoint evaluations. It is expected that the use of further locoregional therapies for new sites of intrahepatic disease relapse outside the original target lesions will be a common event over the course of study.

## Survival status

Survival status will be obtained by the site personnel, when requested periodically by the trial management team, by contacting the participant, checking the participant's hospital records contacting the participant's treating clinician or general practitioner and/or checking publicly available death registries.

## Schedule of Assessments

**Table 4: Schedule of Assessments**

| **ASSESSMENT** | **PRE**  **RANDOMISATION** |  | **END OFTREATMENT** | **FOLLOW UP** | | | | | | | | | | **PROGRESSION^12^** |
| --- | --- | --- | --- | --- | --- | --- | --- | --- | --- | --- | --- | --- | --- | --- |
|  |  |  |  | **Post Treatment** | **Post**  **Randomisation** | | | | | | | | |  |
|  |  |  |  | **4 wks** | **3**  **mo** | **6**  **mo** | **9**  **mo** | **12**  **mo** | **15**  **mo** | **18**  **mo** | **21**  **mo** | **24**  **mo** | **30+**  **mo ^1^** |  |
| **Eligibility confirmation** | ✓ |  |  |  |  |  |  |  |  |  |  |  |  |  |
| **Informed consent** | ✓ |  |  |  |  |  |  |  |  |  |  |  |  |  |
| **Medical History** | ✓ |  |  |  |  |  |  |  |  |  |  |  |  |  |
| **Clinical assessment^2^** | ✓ |  | ✓ | ✓ | ✓ | ✓ | ✓ | ✓ | ✓ | ✓ | ✓ | ✓ | ✓ |  |
| **Concomitant Medications^4^** | ✓ |  | ✓ | ✓ | ✓ | ✓ | ✓ | ✓ | ✓ | ✓ | ✓ | ✓ | ✓ |  |
| **Bloods^5^** | ✓ |  |  | ✓ | ✓ | ✓ | ✓ | ✓ | ✓ | ✓ | ✓ | ✓ | ✓ |  |
| **Hepatitis status^6^** | ✓ |  |  |  |  |  |  |  |  |  |  |  |  |  |
| **Abdominal Imaging ^7,8^** | ✓ |  |  |  | ✓ | ✓ | ✓ | ✓ | ✓ | ✓ | ✓ | ✓ | ✓ |  |
| **Chest Imaging^9^** | ✓ |  |  |  |  |  |  |  |  |  |  |  |  | ✓ |
| **Pregnancy Test^10^** | ✓ |  |  |  |  |  |  |  |  |  |  |  |  |  |
| **Patient Reported Outcomes^11^** | ✓ |  |  | ✓ |  | ✓ |  | ✓ |  | ✓ |  | ✓ | ✓ |  |
| **Adverse Event Reporting**  **(CTCAE v5)** |  |  | ✓ | ✓ | ✓ | ✓ | ✓ | ✓ | ✓ | ✓ | ✓ | ✓ | ✓ |  |
| **Participant experience interview** |  |  |  | ✓**^13^** |  |  |  |  |  |  |  |  |  |  |

**KEY;**

| 1 | Subsequent follow up every 6 months thereafter until study completion |  |
| --- | --- | --- |
| 2 | To include: ECOG Performance status, presence of ascites or encephalopathy, weight, body mass index |  |
| 3 | To confirm absence of uncontrolled ascites or encephalopathy only (ECOG, weight, BMI not required) |  |
| 4 | After disease progression confirmed, only subsequent regimens of anti-cancer therapy will be recorded |  |
| 5 | Includes FBC (Hb, platelets, WCC, neutrophils, lymphocytes), INR, PT/APTT, AST, ALT, ALP, GGT, total bilirubin, albumin, creatinine, sodium and AFP |  |
| 6 | Documentation of hepatitis B & C virological status and need for treatment |  |
| 7 | Multiphase contrast-enhanced CT or MRI of the liver. See Appendix 3 Imaging Guidelines for recommended CT and MRI sequences. |  |
| 8 | For thermal ablation treatments in cohort 1 only, a contrast enhanced CT is required to verify the ablation margin within 24 hours of ablation. See Section 6.1.1 Quality Assurance (QA) measures for MWA/RFA |  |
| 9 | CT chest (+/- pelvis) |  |
| 10 | Women with childbearing potential only. Testing as per institutional protocol. | |
| 11 | EORTC QLQ-C30, QLQ-HCC18 |  |
|  |  |  |
| 12 | Follow-up should continue beyond progression to allow for collection of subsequent therapies, QoL, and second sites of progression |  |
| 13 | If consented, the interview will be conducted by a central designated interviewer within 4 weeks of treatment completion. |  |

# DISEASE PROGRESSION

Participants will undergo regular tumour assessment (multiphase contrast-enhanced CT or MRI of the liver) as per **Table 5: Schedule of Assessments** until disease progression, withdrawal, end of trial, or death, whichever occurs first. See **APPENDIX 3: Imaging Guidelines** for recommendations on specific imaging sequences.

- Baseline tumour measurements must be undertaken prior to any protocol treatment commencing. (see **Figure 2: mRECIST assessment of tumour lesions at baseline** for target lesion definition). The initial assessment of response will be determined after all protocol treatment has been completed, irrespective whether all of the planned treatment was delivered.
- The target lesion is to be assessed by mRECIST and RECIST v1.1 criteria (see sections **8.1 Definition of Progression** and **8.2 Definitions of (non-PD) target lesion** responses and **Figure 3: mRECIST assessment of tumour response**) at each applicable follow-up timepoint until progression.

Local progression is defined as at the first timepoint that either mRECIST **or** RECIST v1.1 criteria for progression are met. In addition, for cohort 1 (thermal ablation verses SABR) local progression will include the development of any new lesions within 10mm of the ablation cavity following thermal ablation or within 15mm of the target lesion following SABR.

In the event of a progression event, or if the investigator is in doubt as to whether progression has occurred, the imaging should be submitted for central radiological review and no further therapy undertaken until unequivocal progression has been confirmed. Repeat imaging at the next scheduled assessment, or sooner if clinically indicated, is recommended for equivocal findings. If subsequent repeat imaging confirms unequivocal progression the date of the initial imaging will be used as the date of progression. Please refer to section 14.7.4 for further details.

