### Post Randomisation

Visits will occur from 3 months post-randomisation in 3 monthly intervals (+/- 2 week) to 2 years and then 6 monthly (+/- 2week) until completion of the trial and are to include;

- Blood tests:
  - Clinical chemistry: AST, ALT, ALP, GGT, total bilirubin, albumin, creatinine, sodium
  - Haematology: Hgb, WCC, Neuts, Lymph, Plts
  - Coagulation: PT, APTT, INR
  - AFP
- Clinical assessment including:
  - ECOG Performance status
  - Presence of ascites or encephalopathy and Child Pugh score
  - Weight and body mass index
  - Adverse event reporting (CTCAE v5.0)
    - *Assessment of toxicity is continuous and will include any event occurring between assessments*.
  - Concomitant medications
  - Recording of any additional investigations or events performed or hospitalisations (required for Health economics analysis)
- Disease assessment:
  - Abdominal Imaging: Multiphase contrast-enhanced CT or MRI of the liver
    - In the individual patient it is recommended that the same imaging modality is used throughout the study for more reliable response assessment.
    - See **APPENDIX 3: Imaging Guidelines** for recommended sequences.
  - See **Section 8 DISEASE PROGRESSION** for further details on assessment for disease progression.

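### Section 8 stops liver imaging at unqualified disease progression, contradicting Sections 7.3.2 and 7.4 and Table 4, and puts ascertainment of 2-year FFLP at risk after relapse outside the target lesion

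*Protocol*

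**What the plan says.** Section 8 (Disease Progression) contains two stop rules. Its opening sentence has participants undergo multiphase liver CT or MRI "until disease progression, withdrawal, end of trial, or death, whichever occurs first". Its second bullet has the target lesion assessed by mRECIST and RECIST v1.1 "at each applicable follow-up timepoint until progression". Neither rule is limited to local progression.

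Three other places continue assessment:

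- Section 7.3.2 sets visits that include liver imaging "in 3 monthly intervals (+/- 2 week) to 2 years and then 6 monthly (+/- 2week) until completion of the trial", with no stop at progression.
- Section 7.4 says: "On-trial assessments should continue beyond progression to allow for collection of subsequent therapies, QoL, and second sites of progression", and names the primary endpoint among the purposes. It also expects that further locoregional therapy for "new sites of intrahepatic disease relapse outside the original target lesions will be a common event over the course of study".
- Table 4, note 12, says: "Follow-up should continue beyond progression to allow for collection of subsequent therapies, QoL, and second sites of progression".

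The primary endpoint (Table 8) is 2-year FFLP, which concerns the treated lesion. In Cohort 1 it also includes a defined margin around the treated area. Section 14.1 inflates the sample for 10% drop-out and 10% mortality, and for nothing else.

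**The concern.** FFLP needs the treated lesion to be imaged for 2 years or until it progresses. A new nodule in another segment is progression of disease but says nothing about the treated lesion. If imaging stops there, any later local failure goes unrecorded.

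The loss then takes one of two forms. If such patients are censored at relapse elsewhere, fewer remain at risk, and the censoring may be related to tumour biology. If they are carried forward as free of local progression, local failure is understated, and by more in absolute terms in the arm with more of it. Scans that were not taken cannot be recovered by any analysis plan.

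**Working it through.** **1. What progression covers in Section 8.** The section deals with the target lesion (8.1.1), with new intrahepatic and extrahepatic lesions (8.1.2), and with both in Table 6. Table 8 defines the PFS event as local progression or new lesions and refers to Section 8 for the definition. Section 8 uses the narrower term, local progression, in the paragraph after the two stop rules. The unqualified term in the opening sentence therefore reads most naturally as the wider one.

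**2. Which rule a site would follow.** Section 8 is mandatory in tone (will). Section 7.4 and Table 4 note 12 say should, and neither names liver imaging. Section 7.3.2 does schedule it, but sends the reader to Section 8 for progression assessment. Section 8 refers to the schedule as Table 5, but Table 5 defines local progression and the schedule is Table 4. The Progression column of Table 4 ticks chest imaging only. No text says which rule prevails.

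**3. The plan's sample size.** Two proportions, 1:1, two-sided alpha 0.05, 80% power, unpooled variance: n = (1.960 + 0.842)² × [p1(1−p1) + p2(1−p2)] / (p1−p2)².

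- Cohort 1 (95% v 75%): 7.849 × (0.0475 + 0.1875) / 0.04 = 46.1, so 47 per arm; 47/0.80 = 58.75, so 59 per arm and 118 in total.
- Cohort 2 (90% v 65%): 7.849 × (0.0900 + 0.2275) / 0.0625 = 39.9, so 40 per arm; 40/0.80 = 50 per arm and 100 in total.

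Both stated figures reproduce. The allowance of 10% + 10% = 20% is used up by drop-out and death.

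**4. Local failures seen before relapse elsewhere.** Assume constant, independent hazards and let b = −ln(1 − non-local progression by 2 years) and a = −ln(1 − local progression by 2 years). The share with local progression first is a/(a+b) × (1 − e^−(a+b)). With an assumed 45% non-local progression, b = 0.598.

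- Thermal ablation, 25% local: a = 0.288; 0.325 × 0.588 = 19.1%.
- SABR, 5% local: a = 0.051; 0.079 × 0.478 = 3.8%.

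**5. Power if every site stops imaging at non-local progression.** Trials were simulated with 59 and 50 per arm, 10% deaths and 10% drop-out by 2 years, and constant independent hazards. The 24-month Aalen-Johansen estimates were compared by a Wald test, with non-local progression acting as censoring. Two separate runs of 2,000 trials per cell gave:

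| Non-local progression by 2 years (assumed) | Cohort 1 | Cohort 2 |
|---|---|---|
| None | 87%, 88% | 84%, 83% |
| 30% | 80%, 82% | 77%, 76% |
| 45% | 76%, 75% | 71%, 71% |
| 60% | 68%, 69% | 66%, 66% |

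The starting values exceed 80% because this model uses all randomised patients up to death or drop-out, while Section 14.1 counts only 47 and 40 evaluable per arm. Treating non-local progression as a competing event instead gives 75% and 74% at the 45% assumption.

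**6. Cross-check with simple proportions.** The pooled-variance formula gives 78% (Cohort 1) and 77% (Cohort 2) at 47 and 40 per arm with no further loss.

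- If 20% of evaluable patients lose their 2-year local status, 47 × 0.8 = 37.6 and 40 × 0.8 = 32 per arm remain, and power is about 69% and 68%.
- If instead patients are carried forward as free of local progression, with 30% progressing elsewhere, the observable difference falls from 20 to 17 points and from 25 to 21 points, and power is about 70% and 69%.

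**The case against.** The strongest reply is that continued imaging was plainly intended. Section 7.3.2 schedules it to trial completion, Section 7.4 gives the primary endpoint as a reason to continue, and Table 4 note 12 repeats the instruction. On this view one sentence is loosely worded, and harm arises only where a site follows it over three contrary provisions. The evidence of intent stands, and it rules out reading the protocol as a deliberate decision to stop at relapse elsewhere. It does not remove the conflict, because the sentence in question is the imaging rule in the section on progression, and nothing ranks it below the others.

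Second, the target-lesion bullet can fairly be read as meaning until the target lesion progresses. That stands. The wider reading is clear only for the opening sentence on imaging. That sentence is enough, since a lesion that is not imaged cannot be assessed.

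Third, a reader might infer that the sample size can no longer deliver 80% power. The documents do not support so general a claim. At the 30% assumption Cohort 1 still has about 80%. The rate itself is assumed: Section 7.4 says only that treatment for such relapse will be common. One ablation series in Table 1 reports 23.4% local recurrence at a mean of 14 months and 30% recurrence-free survival at 3 years, but the time horizons differ, and the series admitted up to three lesions where this trial takes solitary tumours. In addition, independent censoring costs precision but leaves the expected estimate near its true value. Bias from disease-related censoring is possible but is not quantified here.

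**Conclusion.** The contradiction is real and bears on collection of the primary endpoint. As written, a site can comply with Section 8 and yet lose target-lesion status after relapse elsewhere, and the 20% allowance has no room for that loss.

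The size is conditional. With all sites following Section 8 and 30 to 60% non-local progression by 2 years, power is about 80 to 68% in Cohort 1 and 77 to 66% in Cohort 2, against the stated 80%. Partial adherence would lose less, and sites that follow Sections 7.3.2 and 7.4 would lose nothing on this account. The figures also assume constant, independent hazards.

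Two further inferences are not supported. The sample-size arithmetic is not at fault: 118 and 100 reproduce and can stand if imaging continues. Nor does the contradiction settle whether non-local progression, or treatment for it, should censor FFLP. That is an analysis choice which Section 14.6 allows the SAP to detail.

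**What to change.** Reconcile Section 8 with Sections 7.3.2 and 7.4 and Table 4:

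- Scheduled liver imaging continues through follow-up, until withdrawal, death or end of trial, regardless of progression.
- The target lesion is assessed at each scheduled timepoint until local progression, so progression outside it does not end FFLP ascertainment.
- The reference in Section 8 to the Schedule of Assessments is corrected from Table 5 to Table 4.

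Imaging itself should not be made to stop at local progression. That would create a new conflict with Section 7.3.2 and with the collection of second sites of progression in Section 7.4 and Table 4 note 12. The FFLP censoring rule stays with the SAP.

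The cost is a wording amendment and a notice to sites. It adds no visits or scans to the existing schedule and leaves the sample size unchanged.

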## Definition of Progression

### Local progression

Target lesion progression will be assessed by mRECIST and RECIST v1.1. If arterial phase enhancement cannot be used then RECIST v1.1 criteria for progression will apply (see **Table 7: Summary of Response Assessment**).

- For **typical** lesions, local progression is defined by evaluation of the target lesion as measured by mRECIST criteria, i.e. an increase of ≥20% (compared to nadir) in longest diameter of viable arterial enhancing tumour with an absolute increase of ≥5mm, excluding intervening areas of complete necrosis. (43)

The longest viable tumour diameter may or may not be located in the same scan plane in which the baseline longest viable tumour diameter was measured.

- For **atypical** lesions (non-arterially enhancing or rim-enhancing at baseline) or for those lesions with equivocal or discordant central review mRECIST findings, progression according to RECIST v1.1 criteria will also be scored as a local progression event, i.e. an increase of ≥20% (compared to nadir) in longest diameter of the whole target lesion with an absolute increase of ≥5mm. (56)

Equivocal findings or discordant central radiological assessments should be confirmed with interval imaging and additional therapy should not be undertaken until unequivocal progression has been confirmed. Equivocal findings are expected to be more common for the radiation-based therapies (TARE and SABR).

Additionally, for Cohort 1, local progression will include any recurrence within 10mm of the ablation zone for MWA/RFA or within 15mm of the target lesion for SABR.(23) For SABR treatments this will equate to a >10mm margin on the high dose region, i.e the planning target volume (PTV) which itself is a ≥5mm margin on the target lesion. Given there can be significant parenchymal atrophy and contraction around the SABR treated lesion with distortion of liver shape, a direct overlay of the PTV will not accurately depict the treated region over time. Similarly, it is acknowledged that a larger thermal ablation margin or in the case of SABR, the use of larger PTVs or development of larger volumes of off-target parenchymal contraction introduces some variability to this spatial definition.

**Table 5: Definition of Local Progression by Cohort**

| **COHORT AND TREATMENT** | | **BASELINE MEASUREMENT** | **LOCAL PROGRESSION DEFINITION** |
| --- | --- | --- | --- |
| **Cohort 1**  **Comparison** | **MWA/RFA** | Ablation Cavity* | Within 10mm of ablation cavity |
|  | **SABR** | Target lesion | Within 15mm of target lesion |
| **Cohort 2**  **Comparison** | **SOC** | Target lesion | Target lesion |
|  | **SABR** | Target lesion | Target lesion |

*For RECIST V1.1 measurement

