## Challenges in response assessment in hepatocellular carcinoma and across modalities.

Assessment of response and progression poses a number of challenges in the setting of local therapies for early stage HCC.(43, 44) For so called “typical” lesions that display intratumoural (non-rim like) arterial enhancement, complete necrosis of the tumour (as evidenced by a lack of arterial enhancement) following local therapies may be scored as stable disease (SD) via RECIST v1.1 or even progressive disease (PD) if cystic swelling of the necrotic lesion occurs. For thermal ablation, the post-ablation cavity is typically larger than the baseline RECIST v1.1 tumour measurement. Furthermore, the presence of regenerative nodules, post-therapy perfusional changes, ascites, pleural effusions and enlarged peri-portal lymph nodes can all occur in the context of underlying cirrhosis and/or prior therapies in the absence of true disease progression. The modified RECIST (mRECIST) criteria were developed to address the above issues and reduce the overreporting of progressive disease. (43)

mRECIST takes into account the events that can be attributable to the natural history of cirrhosis as above and also introduced the concept of “viable” tumour for response assessment of target lesions. It defines “typical” intrahepatic HCC lesions as ones that demonstrate intratumoural (*i.e.* non-rim-like) arterial enhancement on contrast-enhanced CT or MRI. For typical lesions mRECIST recommends measuring the longest diameter of viable tumour (i.e. any persistent enhancement) instead of overall lesion diameter. Target lesion progression using mRECIST criteria requires at least a 20% increase (compared to nadir) in longest diameter of viable arterial enhancing tumour with an absolute increase of ≥5mm. This measurement should exclude intervening areas of complete necrosis. A new typical intrahepatic lesion must be ≥1cm. This has been shown to be a more accurate predictor of response and progression for typical lesions treated with thermal ablation or TACE. (43)

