Despite the above challenges in assigning various categories for response such as stable disease, partial or complete response, the endpoint of progressive disease appears to be more reliable. The primary endpoint of the SOCRATES study will be FFLP with local progression defined as target lesion progression as per mRECIST criteria (viable tumour diameter for typical lesions, lesion diameter for atypical lesions). Given the potential for more complex vascular changes following radiation-based therapies, RECIST v1.1 measurements will also be taken and local progression events will also include progression on RECIST v1.1. criteria. For the thermal ablation cohort, the post-ablation cavity will serve as baseline for RECIST v1.1 measurements. Central, independent radiological review will be undertaken for progression events with equivocal findings or non-consensus regarding progression requiring interval imaging to confirm progression (backdated to the previous imaging time point).

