### Cohort 2 participants

- MWA or RFA may be used in cohort 2 for tumours >3cm if this represents standard of care therapy at the institution. It may be combined with transarterial therapies. All therapy is required to be completed within the primary therapy window of within 42 days from randomisation.
- MWA or RFA is not allowed for tumours ≤3cm in cohort 2 as this is a specific exclusion criteria for cohort 2. These patients are eligible for cohort 1.
- Technique will be as per local departmental protocols.

#### QA Measures for MWA or RFA in cohort 2

- Collection of treatment reports and mode of ablation (MWA v RFA, CT v USS-guided)
- Immediate post-ablation imaging and margin assessment will be as per departmental protocols and will not be assessed centrally for cohort 2.
  - Please see **APPENDIX 3: Imaging Guidelines** for recommendations on specific imaging sequences.

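### Table 5 gives ablated Cohort 2 patients no post-ablation-cavity baseline, so under Section 8's either-criterion rule a successful ablation could be scored as local progression, in the SOC arm only

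*Protocol*

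**What the plan says.** **Baseline.** Section 8 states that "Baseline tumour measurements must be undertaken prior to any protocol treatment commencing". Table 5 makes one exception, the Cohort 1 MWA/RFA row: "Ablation Cavity* | Within 10mm of ablation cavity", where the asterisk marks the cavity as the RECIST v1.1 baseline. The Cohort 2 SOC row reads "SOC | Target lesion | Target lesion", with no cavity and no asterisk; its entries, "Target lesion | Target lesion", are the same as those of the SABR row. Section 1.6 gives the matching rule: "For the thermal ablation cohort, the post-ablation cavity will serve as baseline for RECIST v1.1 measurements".

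**Ablation in Cohort 2.** Section 6.1.2 says "MWA or RFA may be used in cohort 2 for tumours >3cm if this represents standard of care therapy at the institution", and allows it together with transarterial therapy. Section 6 names TACE-RFA for tumours above 3 cm as an example, and Section 10.1 lists combined TACE and ablation among the four main treatments anticipated. On imaging, Section 6.1.2 adds: "Immediate post-ablation imaging and margin assessment will be as per departmental protocols and will not be assessed centrally for cohort 2".

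**The hazard.** Section 1.6 notes that after thermal ablation "the post-ablation cavity is typically larger than the baseline RECIST v1.1 tumour measurement".

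**When RECIST v1.1 counts.** The protocol gives two rules.
- Broad: Section 8 (opening text) dates local progression from the first timepoint at which either mRECIST or RECIST v1.1 is met. Section 1.6 likewise adds RECIST v1.1 progression to the local progression events.
- Narrow: Table 2 uses RECIST v1.1 only when mRECIST cannot be used. Section 8.1.1 and Table 6 use it for atypical lesions or when mRECIST is equivocal or discordant, and Section 8.1.1 also when arterial enhancement cannot be used. Table 8 refers the primary endpoint to Section 8.1.

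**The concern.** The protocol identifies a measurement artefact of thermal ablation and removes it for Cohort 1. It leaves the artefact in place for Cohort 2, where the same procedure is allowed in one arm. An ablation zone that properly covers the tumour plus a margin is larger than the tumour. Measured against the pre-treatment tumour, it can cross the RECIST v1.1 growth threshold with no viable disease.

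The primary endpoint, 2-year FFLP, is at stake. Only the SOC arm of Cohort 2 can receive ablation as primary therapy, so false events of this kind can occur only there. They lower SOC FFLP and favour SABR. Patients treated with TACE or TARE alone are not affected.

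**Working it through.** **Plan's own figure.** Section 14.1: 90% v 65%, two-sided alpha 0.05, 80% power, 40 evaluable per arm. The unpooled normal formula gives (1.960 + 0.842)² × (0.90×0.10 + 0.65×0.35) / 0.25² = 39.9, so 40. The plan's figure reproduces and is not in dispute; n = 40 per arm is used below.

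**Step 1: does a successful ablation cross the threshold?**

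Inputs:
- RECIST v1.1 progression: at least +20% and at least +5 mm over nadir (Section 8.1.1).
- Nadir: the pre-treatment diameter D, as Table 5 and Section 8 imply for Cohort 2.
- Tumours above 30 mm (Section 6.1.2) and up to 80 mm (Section 4.3.1).
- Margin m per side: no figure is given for Cohort 2. The Cohort 1 aim is above 5 mm (Section 6.1.1). Margins of 5 and 10 mm are assumed here.

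Cavity = D + 2m, and relative growth = 2m/D.

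| D (mm) | m = 5 mm | meets criterion | m = 10 mm | meets criterion |
|---|---|---|---|---|
| 31 | 41 mm, +32% | yes | 51 mm, +65% | yes |
| 35 | 45 mm, +29% | yes | 55 mm, +57% | yes |
| 40 | 50 mm, +25% | yes | 60 mm, +50% | yes |
| 50 | 60 mm, +20% | yes | 70 mm, +40% | yes |
| 55 | 65 mm, +18% | no | 75 mm, +36% | yes |
| 80 | 90 mm, +12.5% | no | 100 mm, +25% | yes |

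The absolute increase is 10 mm or 20 mm, so the 5 mm condition is always met. The binding condition is 2m/D ≥ 0.20, that is m ≥ 10% of D: 3.1 mm at D = 31, 5 mm at D = 50, 8 mm at D = 80.

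**Step 2: does crossing it make an event?**
- Broad rule (Sections 8 and 1.6): yes, for any lesion in Step 1 that meets the criterion.
- Narrow rule (Table 2, Section 8.1.1, Table 6): only for atypical lesions or where mRECIST is equivocal, discordant or unusable. A typical lesion with no residual arterial enhancement is not progression.

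**Step 3: what could it do to the comparison?** Let s be the share of all SOC patients falsely scored, assumed to have the same true FFLP as the rest of the arm. Scored SOC FFLP = true FFLP × (1 − s). The documents do not give s. The last column is the exact binomial probability that a two-sided z-test at 0.05 rejects, with n = 40 per arm, SABR at 90%, and SOC truly at 90%.

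| s | Scored SOC FFLP if truly 65% | if truly 90% | Chance of a significant result, both truly 90% |
|---|---|---|---|
| 0 | 65% | 90% | 5.9% |
| 2% | 63.7% | 88.2% | 6.6% |
| 5% | 61.8% | 85.5% | 10% |
| 10% | 58.5% | 81% | 21% |
| 20% | 52% | 72% | 56% |

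The right comparator is 5.9%, this test's own rate with no mis-scoring, and not the nominal 5%. As examples of s: if 20% of the arm is ablated and 10% of those are exposed under the narrow rule, s = 2%; if 20% is ablated and every one is mis-scored, s = 20%.

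**After the change.** With the cavity as baseline the first post-ablation change is 0 mm and 0%, so ablation alone creates no event. The sample size is unchanged.

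**The case against.** The strongest reply is that the narrow rule is the operative one. It appears in the primary-endpoint row of Table 2, in Section 8.1.1 and in Table 6, and Table 8 refers to Section 8.1. Under it a fully ablated typical lesion has no viable enhancement and is not progression, which is the reason Section 1.6 gives for using mRECIST. This stands as a limit on the effect. It does not close the gap: the opening of Section 8 and Section 1.6 state the opposite rule, and atypical or equivocal lesions are exposed under both.

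Second, every triggered event goes to central review (Sections 8 and 15.7.4). Section 5.5 says reviewers cannot reliably be blinded, so they may recognise an ablation zone and reject the event. Some events would probably be stopped this way. But nothing tells reviewers to measure from the cavity in Cohort 2, and immediate post-ablation imaging there is not assessed centrally. The correction would be discretionary and made by unblinded readers.

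Third, the phrase in Section 1.6 about the thermal ablation cohort could mean all ablated patients. Table 5 makes Cohort 1 the likelier reading. The ambiguity itself calls for clarification.

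A reader might infer that every successful ablation in Cohort 2 would be scored as progression. The documents do not support that. It requires the broad rule, a margin of at least 10% of the diameter per side, and no rejection at review.

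**Conclusion.** The gap is real and should be fixed. As written, Table 5 and the opening of Section 8 together allow a successful ablation to count as a primary-endpoint event, in one arm of Cohort 2 only and in SABR's favour. With an assumed margin of at least 5 mm per side this applies to tumours of 31 to 50 mm; larger tumours need a margin of at least 10% of the diameter. Under the narrow rule only atypical lesions, or those with equivocal, discordant or unusable mRECIST, are exposed.

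The size is uncertain. It depends on the share of SOC patients ablated, the rule applied, and how many events review rejects. The documents give neither the ablated share nor the rejection rate. The range from 6.6% (2% mis-scored) to 56% (20% mis-scored), against 5.9% with none, shows how sensitive the comparison is and is not a forecast. A reader might take 56% as the trial's false-positive rate. It is an upper bound for an assumed 20% ablated share with every ablation mis-scored, and it also supposes 90% FFLP in both arms, whereas Section 14.1 plans 65% for SOC.

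**What to change.** 1. In Table 5 (SOC row and footnote) and Section 1.6, extend the existing cavity baseline for RECIST v1.1 to every patient treated with MWA/RFA in either cohort, including TACE plus ablation. Take it from the first post-treatment scan, or from the scheduled 3-month scan if there is none earlier. Add the same exception to the baseline sentence in Section 8.
2. Reconcile Section 1.6 and the opening of Section 8 with Table 2, Section 8.1.1 and Table 6, so that one rule states when RECIST v1.1 alone makes a local progression event. Step 1 alone would leave this contradiction standing.
3. Require the cavity-baseline scan to be submitted with any Cohort 2 progression in an ablated patient sent for central review.
4. Re-check Cohort 2 ablation events already scored.

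The cost is a short amendment and one extra image upload per affected event. No treatment, visit or sample size changes. The drawback is that, where the 3-month scan serves as baseline, very early true growth is absorbed into it and may be missed by RECIST v1.1.
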